### 5.2. Treatment Assignment

All Subjects will be assigned to receive 160 mg of EC micronised free-base darapladib as a single dose and as repeated daily doses for 28 days.

### 5.3. Subject Specific Dose Adjustment/Stopping Criteria

#### 5.3.1. Liver Chemistry Stopping Criteria

Liver chemistry threshold stopping criteria have been designed to assure Subject safety and to evaluate liver event etiology (in alignment with the FDA premarketing clinical liver safety guidance).

Study treatment will be stopped for a Subject if the following liver chemistry stopping criteria is met:

- Alanine aminotransferase (ALT)  $\geq 3 \times \text{ULN}$

NOTE: Refer to [Appendix 1](#) for details of the required assessments if a Subject meets the above criteria.

#### 5.3.2. QTc Withdrawal Criteria

A Subject that meets either criterion below will be withdrawn from the study. The QT correction formula used to determine discontinuation should be the same one used throughout the study.

- QTc > 500 msec

If a Subject has underlying bundle branch block the following withdrawal criteria should be used instead:

| Baseline QTc value (with underlying bundle branch | QTc withdrawal criteria |
|---------------------------------------------------|-------------------------|
| <450 msec                                         | >500 msec               |
| 450-480 msec                                      | ≥530 msec               |

Withdrawal of Subjects is to be based on an average QTc value of triplicate ECGs. If an ECG demonstrates a prolonged QT interval, then obtain 2 more ECGs at different timepoints more than 5 minute apart after 15 minutes rest and then use the averaged QTc values of the 3 ECGs to determine whether the Subject should be discontinued from the study

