| Primary                                                                                                                                                                                                                                                                                                                                                                                           |                                                                                                                                                                                                                                                                                                                                                                                                                                                                                                                                                                                                                                                                                                                                                                                                          |
| 
 
1. To assess the safety and tolerability of single and repeat oral dose of 160 mg EC darapladib in healthy Chinese Subjects.
 
2. To assess the primary PK parameters of single and repeat oral dose of 160 mg EC darapladib in healthy Chinese Subjects.
 
                                                                                       | 
 
1. Clinical safety data from spontaneous AE reporting, 12-lead electrocardiogram (ECG) recording, vital sign measurement, nursing/physician observation and clinical laboratory examination will be summarized and any clinically significant abnormalities described.
 
2. The primary PK endpoints of interest are area under the concentration-time curve from time zero (pre-dose) to last time of quantifiable concentration (AUC[0-t]), area under the concentration-time curve from time zero (pre-dose) extrapolated to infinite time (AUC [0-∞]), maximum observed concentration (Cmax) and accumulation ratios (Cmax accumulation ratio [Rcmax] and observed accumulation ratio [Ro]) of darapladib.
 
 |

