### **3. STUDY DESIGN**

#### **3.1. Study Design Detail**

This will be an open label study where each Subject will participate in 2 study sessions (single and repeat dose). All Subjects will receive 160 mg EC micronised free-base darapladib as a single dose and as repeated daily dose for 28 days. There will be at least 4 days between dosing in the Single Dose Session and the first dose of the Repeat Dose Session due to the 96-hour PK sampling period following the single dose. PK samples will be collected over a 96-hour period after single dose in Session 1, and over a 24-hour period after Day 28 of repeat dosing, as well as over a 28-day duration following the last day of dosing of the repeat dose session. PD samples will be collected over a 24-hour period after Day 28 of repeat dosing, as well as over the 28-day duration following the last day of dosing of the repeat dose session.

Subjects will return approximately 28 days after the last dose of study medication for a follow-up visit. The total study duration for each Subject including the Screening, Treatment and Follow-up periods will be approximately 12 weeks.

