##### **3.2.2. Dose Rationale**

As of December 2011, a total of approximately 652 healthy volunteers and 1179 patients from completed clinical trials had received darapladib. In overseas studies single and repeat oral QD doses of up to 100 mg of the non-EC freebase formulation and up to 480 mg of the EC free base micronised formulation of darapladib have been administered. Darapladib has been well tolerated. Mean half-life of darapladib was 126 hours following QD dosing of 160 mg EC tablets of micronised free-base darapladib to healthy western Subjects (Protocol Number LPL112498). Darapladib is expected to reach its steady state following repeat dosing of 28 days.

Study LPL110736, a double blind, randomized, parallel, placebo-controlled study, was conducted in Japan to investigate the safety, tolerability, PK and PD following 160 mg enteric coated, micronized free-base daily doses of darapladib in healthy Japanese male Subjects for 12 days. A substantial inter-ethnic difference in darapladib PK and PD was not observed.

Based on these data, this study will be conducted to determine the safety/tolerability, PK and PD of the EC, free base micronised darapladib 160 mg in the single dose session and repeat dose session in healthy Chinese Subjects. EC free base (micronised) darapladib 160 mg in this study is currently being evaluated in the ongoing global phase III studies of darapladib.

Darapladib will be administered as EC tablets formulated to begin disintegration at pH 5.5 and above. Under these conditions, the formation of 4-fluorobenzyl chloride, a potential alkylating agent that is an acid degradation product of darapladib that is formed only at very low pH in the presence of chloride ions, is anticipated to be negligible at this proposed dose.

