### **5.3.3. Other Dose Adjustment/Stopping Safety Criteria**

For an individual study participant, stopping criteria include, but are not limited to:

Severe signs or symptoms, or significant changes in any of the safety assessments, that put the safety of the individual at risk (e.g. ECG, vital signs, laboratory tests, etc), as judged by the Principal Investigator in consultation with the Medical Monitor if necessary.

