## 6. STUDY ASSESSMENTS AND PROCEDURES

This section lists the procedures and parameters of each planned study assessment. The exact timing of each assessment is listed in the Time and Events Table Section 6.1. Whenever vital signs, 12-lead ECGs and blood draws are scheduled for the same nominal time, the assessments should occur in the following order: 12-lead ECG, vital signs, and blood draws.

Protocol waivers or exemptions are not allowed with the exception of immediate safety concerns. Therefore, adherence to the study design requirements, including those specified in the Time and Events Table, are essential and required for study conduct.

The timing and number of planned study assessments, including safety, PK, PD assessments may be altered during the course of the study based on newly available data (e.g. to obtain data closer to the time of peak plasma concentrations) to ensure appropriate monitoring. The change in timing or addition of time points for any planned study assessments must be approved and documented by GSK, but this will not constitute a protocol amendment. Any safety issues that require alteration of the safety monitoring scheme should be approved by the Institutional Review Board/Independent Ethics Committee (IRB/IEC). There will be 43 time points for PK blood sample collection and approximately 2 mL of blood will be collected each time. There will be 29 time points for PD blood sample collection and approximately 2 mL of blood will be collected each time. Haematological and chemical assessment will be tested for 5 times, 4 mL of blood will be collected for each test. Virological assessment will be tested for 1 time, 3 mL of blood will be collected. 2 ml of blood will be collected for blood pregnancy test at screening for female subjects. Approximately 180 mL of blood will be collected over the duration of the study. If Investigator consider that additional safety assessment is needed, extra blood sample may be required. Venous indwelling needle can be used due to frequently blood sampling in single dose session Day 1 and repeated dose session Day 28. The additional blood loss may be 10ml.

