| Meal              | X       | X    | X    | X    | X    | X    | X    | X    | X    | X     | X     | X     | X     | X              | X     | X     | X     | X     | X     | X     | X     | X     | X     | X     | X     | X              | X              | X              |
| PK Blood Samples              |         |      |      |      |      |      |      |      |      |       |       |       |       | X  |       |       |       |       |       |       |       |       |       |       |       | X  | X  | X  |
| PD Blood Samples              |         |      |      |      |      |      |      |      |      |       |       |       |       | X  |       |       |       |       |       |       |       |       |       |       |       | X  | X  | X  |

1. A standard breakfast will be provided and given approximately 1 hour before dosing at each of the outpatient visits.
2. Day 14, Day 26 and Day 27 of repeat dosing require trough (predose) PK and PD samples
3. Samples will be obtained at 0, 0.5, 1, 2, 3, 4, 6, 9, 12, 15, 24 hours post dose

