### **6.3.3. Electrocardiogram**

- 12-lead ECGs will be obtained at designated timepoint during the study outlined in Section 6.1 using an ECG machine that automatically calculates the heart rate and measures PR, QRS, QT, and QTc intervals. Refer to Section 5.3.2 for QTc withdrawal criteria and additional QTc readings that may be necessary.

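### No 12-lead ECG is scheduled during the 28 days of repeat dosing, so the QTc withdrawal rule has no planned measurement to act on for 28 of the 29 doses

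*Combined protocol and SAP*

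**What the plan says.** Section 5.3.2 withdraws a subject whose QTc exceeds 500 msec, with separate limits for bundle branch block: "A Subject that meets either criterion below will be withdrawn from the study". The decision uses the mean of three ECGs, and the process starts when one ECG shows prolongation. Section 5.3.3 adds a judgement-based rule covering severe signs or symptoms, or "significant changes in any of the safety assessments, that put the safety of the individual at risk", and gives ECG as an example of such an assessment.

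On timing, Section 6.3.3 says "12-lead ECGs will be obtained at designated timepoint during the study outlined in Section 6.1". The three tables in Section 6.1 then give:

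- **Single Dose Session:** ECG at screening, Day 1 pre-dose, 4 h, 24 h and 96 h.
- **Repeat Dose Session (RD1 to RD28):** no ECG row. Vital signs are taken on RD14 and RD28, and adverse event review is ongoing.
- **After the last repeat dose:** one ECG, in the follow-up column.

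Section 3.1 places that last occasion: "Subjects will return approximately 28 days after the last dose of study medication for a follow-up visit". The first primary objective in Section 2 is "To assess the safety and tolerability of single and repeat oral dose of 160 mg EC darapladib in healthy Chinese Subjects", and its endpoint names 12-lead ECG recording.

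**The concern.** A stopping rule protects subjects only if the measurement that triggers it is taken while there is still something to stop. Here the scheduled ECGs cover one dose and then a nearly complete washout. They skip the period when exposure is highest and dosing can still be halted. A subject without symptoms whose QTc passed the threshold during repeat dosing would not be found by any planned assessment and would go on receiving tablets.

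The report is affected too. The study is meant to supply safety data supporting later work in Chinese patients (Section 1.1), and Section 8.3.2.2 plans to set the safety results against other studies because there is no placebo group. For ECG under repeat dosing there would be no scheduled data to compare.

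**Working it through.** **1. Are the tables complete as read?** The protocol states no ECG count, but Section 6 states the numbers of PK, PD and laboratory occasions, and the Section 6.1 tables can be checked against them.

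- PK: 15 (single dose) + 3 (RD14, RD26 and RD27 troughs) + 11 (RD28, 0 to 24 h) + 14 (36 to 672 h) = 43; stated 43.
- PD: 1 + 3 + 11 + 14 = 29; stated 29.
- Laboratory: screening, Day -1, 24 h, 96 h and follow-up = 5; stated: "Haematological and chemical assessment will be tested for 5 times".

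All three agree, so a row lost in conversion is unlikely. The amendment log shows no repeat-dose ECG added or removed.

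**2. ECG count.** Screening, pre-dose, 4 h, 24 h, 96 h and follow-up = 6 occasions. In RD1 to RD28: 0. On Days 29 to 56: 0.

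**3. Doses beyond reach of a scheduled ECG.** Total doses are 1 + 28 = 29. RD1 is at least 4 days after the single dose, so the 96 h ECG falls at or before RD1, and all 28 repeat doses come after it.

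**4. Gap between consecutive scheduled ECGs.** RD1 to RD28 is 27 days, plus about 28 days to follow-up: at least about 55 days, or roughly 8 weeks.

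**5. Can the follow-up ECG stand in?** Section 3.2.2 reports: "Mean half-life of darapladib was 126 hours following QD dosing of 160 mg EC tablets". With simple exponential decline, 28 days = 672 h, 672/126 = 5.33 half-lives, and 0.5^5.33 = 0.025. About 2.5% of the end-of-dosing concentration remains.

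**6. Can the single-dose ECGs stand in?** The documents give no accumulation ratio. Assuming one-compartment behaviour with dosing interval τ = 24 h and k = ln 2 / t½, exposure on RD28 relative to the single dose is (1 − e^(−28kτ)) / (1 − e^(−kτ)). The 126 h value is the protocol's; the shorter half-lives are assumed, to show the range. The last column is the fraction of steady state just before the RD14 dose, after 13 doses: 1 − e^(−13kτ).

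| Effective half-life | RD28 / single dose | Fraction of steady state before RD14 dose |
|---|---|---|
| 24 h (assumed) | 2.0 | >0.99 |
| 48 h (assumed) | 3.4 | 0.99 |
| 72 h (assumed) | 4.8 | 0.95 |
| 126 h (Section 3.2.2) | 7.9 | 0.82 |

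Even at the low end, RD28 exposure is twice that covered by the Day 1 ECGs. An ECG before the RD14 dose would be taken at 82% or more of steady state, with 15 doses (RD14 to RD28) still to give.

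**The case against.** The strongest reply is that nothing in the protocol marks QT prolongation as a known risk of darapladib. Table 1 lists 4-FBCl, PAF accumulation and carcinogenicity; EC doses up to 480 mg have been given; the Phase III trials at 160 mg randomised 15,828 and 13,027 subjects, with 813 from China; and the design repeats an earlier western study. ECG frequency in a bridging study is then a risk-based choice. It is true that no QT signal is alleged here, which is why this is a recommended change rather than a critical one. But the protocol reports no QT results and gives no reason for omitting on-treatment ECGs, while keeping both a QTc withdrawal rule and an ECG endpoint for repeat dosing.

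Second, the rule is not wholly idle. Single-dose ECGs can remove a subject before RD1, and Section 5.3.3 can act on symptoms during daily attendance. That stands, but the single-dose ECGs precede all repeat-dose exposure, and symptoms do not reveal asymptomatic prolongation.

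Third, Sections 6 and 6.3 let safety time points be added, and Section 6 says this need not be an amendment. Both tie additions to newly available data, so neither schedules an ECG.

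Fourth, 24 uncontrolled subjects give limited support for any ECG conclusion. Agreed; but limited data are more than none. The table check in step 1 is also indirect, since no ECG total is stated.

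**Conclusion.** The concern holds. None of the six scheduled ECG occasions falls in the Repeat Dose Session, 28 of 29 doses follow the last scheduled ECG that could stop treatment, and the next comes about 8 weeks later. Only an unscheduled ECG could trigger Section 5.3.2 during repeat dosing, and the ECG part of the repeat-dose safety endpoint has no scheduled on-treatment data.

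These counts come straight from the Section 6.1 tables and need no pharmacokinetic assumption. The 2.5% residual and the 2.0- to 7.9-fold exposure range do: they assume one-compartment kinetics, and either the western 126 h half-life or the assumed shorter ones. They explain why neither the follow-up nor the single-dose ECGs can substitute, but the gap does not depend on them.

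**What to change.** Add a 12-lead ECG row to the Repeat Dose Session table at RD14 pre-dose, RD28 pre-dose and RD28 4 h post-dose, and add an ECG on Day 29, 24 h after the last dose, to the table that follows. Apply Section 5.3.2, with its triplicate confirmation, at each. RD14 is early enough to withhold 15 doses. The RD28 4 h and 24 h ECGs match the Day 1 times, so QTc change can be summarised for repeat against single dosing.

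The cost is 4 × 24 = 96 ECG occasions, plus repeats for any prolonged value. No visit is added: subjects attend daily for dosing, as the table's meal note reflects ("A standard breakfast will be provided and given approximately 1 hour before dosing at each of the outpatient visits"), and are inpatients from RD27 until discharge on Day 30. A standing change to the schedule calls for an amendment to Section 6.1.

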### **5.3.3. Other Dose Adjustment/Stopping Safety Criteria**

For an individual study participant, stopping criteria include, but are not limited to:

Severe signs or symptoms, or significant changes in any of the safety assessments, that put the safety of the individual at risk (e.g. ECG, vital signs, laboratory tests, etc), as judged by the Principal Investigator in consultation with the Medical Monitor if necessary.

### **5.4. Blinding**

This will be an open-label study.

### **5.5. Packaging and Labeling**

The contents of the label will be in accordance with all applicable regulatory requirements.

### **5.6. Preparation/Handling/Storage/Accountability**

No special preparation of study treatment is required.

Study treatment must be dispensed or administered according to procedures described herein. Only Subjects enrolled in the study may receive study treatment. Only authorized site staff may supply or administer study treatment. All study treatment must be stored in a secure area with access limited to the Investigator and authorized site staff. Study treatment is to be stored up to 30°C, protected from light and moisture. Maintenance of a temperature log (manual or automated) is required.

The Investigator, institution, or the Head of the medical institution (where applicable) is responsible for study treatment accountability, reconciliation, and record maintenance. The Investigator or the Head of the medical institution (where applicable), or designated site staff (e.g., storage manager, where applicable) must maintain study treatment accountability records throughout the course of the study. The responsible persons will document the amount of study treatment received from and returned to GSK and the amount administered to Subjects. The required accountability unit for this study will be tablet. Discrepancies are to be reconciled or resolved. Unused investigational products

will be returned to and destroyed by GSK. Procedures for final disposition of unused study treatment are listed in the SPM.

Investigational product is not expected to pose significant occupational safety risk to site staff under normal conditions of use and administration. A Material Safety Data Sheet (MSDS)/equivalent document describing occupational hazards and recommended handling precautions either will be provided to the Investigator, where this is required by local laws, or is available upon request from GSK.

Precaution will be taken to avoid direct contact with the investigational product. A MSDS describing occupational hazards and recommended handling precautions will be provided to the Investigator.

## **5.7. Assessment of Compliance**

When the individual dose for a Subject is prepared from a bulk supply, the preparation of the dose will be confirmed by a second member of the study site staff.

When Subjects are dosed at the study site, they will receive study treatment directly from the Investigator or designee, under medical supervision. The date and time of each dose administered in the clinic will be recorded in the source documents. The dose of study treatment and study participant identification will be confirmed at the time of dosing by a member of the study site staff other than the person administering the study treatment. Study site personnel will examine each Subject's mouth to ensure that the study treatment was ingested.

## **5.8. Treatment of Study Treatment Overdose**

For this study, any dose of darapladib >160 mg within a 24 hour time period ( $\pm$  1 hour) will be considered an overdose.

GSK does not recommend specific treatment for an overdose. The Investigator will use clinical judgment to treat any overdose.

## **5.9. Treatment After the End of the Study**

Subjects will not receive any additional treatment from GSK after completion of the study because only healthy volunteers are eligible for study participation.

## **5.10. Concomitant Medications and Non-Drug Therapies**

### **5.10.1. Permitted Medications**

Paracetamol at doses of  $\leq$ 2 grams/day is permitted for use any time during the study. Other concomitant medication may be considered on a case by case basis by the (Investigator in consultation with the GSK Medical Monitor [if required]).

**5.10.2. Prohibited Medications and Non-Drug Therapies**

Subjects must abstain from taking prescription or non-prescription drugs (including vitamins and dietary or herbal supplements), within 7 days (or 14 days if the drug is a potential enzyme inducer) or 5 half-lives (whichever is longer) prior to the first dose of study medication until completion of the Follow-up visit, unless in the opinion of the Investigator and Sponsor the medication will not interfere with the study.

## 6. STUDY ASSESSMENTS AND PROCEDURES

This section lists the procedures and parameters of each planned study assessment. The exact timing of each assessment is listed in the Time and Events Table Section 6.1. Whenever vital signs, 12-lead ECGs and blood draws are scheduled for the same nominal time, the assessments should occur in the following order: 12-lead ECG, vital signs, and blood draws.

Protocol waivers or exemptions are not allowed with the exception of immediate safety concerns. Therefore, adherence to the study design requirements, including those specified in the Time and Events Table, are essential and required for study conduct.

The timing and number of planned study assessments, including safety, PK, PD assessments may be altered during the course of the study based on newly available data (e.g. to obtain data closer to the time of peak plasma concentrations) to ensure appropriate monitoring. The change in timing or addition of time points for any planned study assessments must be approved and documented by GSK, but this will not constitute a protocol amendment. Any safety issues that require alteration of the safety monitoring scheme should be approved by the Institutional Review Board/Independent Ethics Committee (IRB/IEC). There will be 43 time points for PK blood sample collection and approximately 2 mL of blood will be collected each time. There will be 29 time points for PD blood sample collection and approximately 2 mL of blood will be collected each time. Haematological and chemical assessment will be tested for 5 times, 4 mL of blood will be collected for each test. Virological assessment will be tested for 1 time, 3 mL of blood will be collected. 2 ml of blood will be collected for blood pregnancy test at screening for female subjects. Approximately 180 mL of blood will be collected over the duration of the study. If Investigator consider that additional safety assessment is needed, extra blood sample may be required. Venous indwelling needle can be used due to frequently blood sampling in single dose session Day 1 and repeated dose session Day 28. The additional blood loss may be 10ml.

